### Allocation of interventions

After informed consent is obtained, participants will be randomized to intervention and placebo control groups 1:1, according to a blocked randomization list (4 patients per block), generated in SAS proc PLAN by an individual at the University Health Network not involved in conducting or analyzing the study. Both the participant and study team, except for the lab technologist, will be blinded to group interventions. The allocation list will be kept in sequentially numbered envelopes with the group assignments. The lab technologist will maintain allocation concealment and prepare fecal filtrates for each patient but not be involved in any other part of the study. The researcher performing FMT will receive the designated fecal filtrate labeled only with the participants’ numbers. If an adverse event occurs that is thought to be potentially linked to FMT and requires immediate investigation, the code will be broken only for the affected patient. Only the study physician with the applicable expertise will be unblinded; the rest of the study team will not be informed.

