### Intervention

Each participant receives one dose of either autologous or allogenic FMT product. FMT manufacturing will be performed as in a previous RCT (NCT01226992). Briefly, 50 g of screened donor or participant feces will be homogenized for 30 min using a Stomacher® Paddle Blender with 30 mL sterile 0.9 % NaCl + 10% glycerol in a sterile, 330-μn microfilter-separated, double-compartment polyethylene bag. The autologous FMT control arm is essential because bowel preparation and colonoscopy can induce changes to the intestinal microbiome [22, 23]. The volume of fecal filtrate corresponding to 50 g of original feces will be aliquoted, labeled with a recipient ID number to maintain blinding, and stored at – 80 °C. Freezing stool with glycerol as a cryoprotectant has been shown to yield active FMT preparations [24, 25]. For instance, frozen fecal filtrate for treatment of *Clostridium difficile* infection can be stored for at least 6 months in 10% glycerol without loss of clinical efficacy or viability of the six bacterial groups measured [26]. Similarly, clinical efficacy in treating *C. difficile* infection was shown not to differ between frozen and lyophilized FMT product after 9, 11, or 15 months [27]. An aliquot of the final fecal filtrate will be stored at – 80 °C for analysis in case retroactive testing of the fecal filtrate is required.

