### Statistical methods

We will use descriptive methods to estimate feasibility and compliance with the FMT intervention, the number of FMT and placebo treatments, the number of fecal samples provided, the duration of follow-up, recruitment rate, rates of nonparticipation, and so on. We will calculate acceptability using reported side effects and patient outcomes.

Variable distribution will be assessed using graphical methods and descriptive statistics, including means, standard deviations, medians and 1st and 3rd quartiles, frequencies and proportions, will be calculated where appropriate. Randomized groups will be compared to assess whether imbalance in covariates such as age and gender are present. For continuous measures (e.g., MADRS scores), change scores will be calculated as the difference between baseline and 6-month visit assessments. Groups will be compared using independent samples *t* test or Wilcoxon signed rank test as appropriate. For binary measures (e.g., proportion of side effects), the difference between groups will be tested using Chi-square or Fisher exact test as appropriate. Bivariate relationships between outcome measures and changes in microbiome composition (e.g., relative abundances of taxa of interest) will be explored using Spearman and Pearson correlation coefficients. For microbiome and metabolome data, multivariate dimensionality reduction approaches, such as Principal Components analysis and cluster analysis, will be employed.

Trajectory plots will be created to examine changes in outcome measures over time. Generalized linear regression models will then be used to assess differences [43] between groups at different time points, as was well as to explore the relationship between these changes and microbiome characteristics. In order to account for correlation between time points, random effects models and generalized estimating equations approach will be used. All models will include group, time, and group by time interaction terms; additionally, factors with known influence on outcome measures will be considered for inclusion as covariates, particularly if found imbalanced between the randomized groups. For patient dropout, the missingness patterns will be assessed, and appropriate methods of handling missing data will be used [44]. Goodness-of-fit will be applied for model diagnostics.

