Statistical analyses will be performed using SAS 9.4, R 3.1, as well as analytic tools available in QIIME package. All tests will be two-sided with a significance level of 5%. Where necessary, *p* value adjustments for multiple testing (e.g., Bonferroni, Holm’s Bonferroni Step-down, Benjamini and Hochberg False Discovery Rate) will be employed.

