### Sample size

This is a pilot feasibility trial designed to show if a larger RCT trial would be worthwhile. Therefore, no formal sample size calculation has been carried out [45]. A review by Hertzog suggests a range of 20 to 40 participants to allow for sufficient variability in acceptability assessment of an intervention [46]. Based on work from a pharmaceutical study in a similar patient population [47], the expected standard deviation of change expected in the MADRS score is approximately 12. Therefore, with 25 patients per group, we will be able to quantify the difference in change in MADRS score between groups to within 6.5 points with 95% confidence. This will allow data that can be used in the generation of a sample size for a larger trial. To account for a 15% dropout rate, we plan to recruit 60 patients; 30 will receive the active treatment (allogenic FMT), and 30 will receive the control treatment (autologous FMT).

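### The non-parametric fallback named for comparing the two randomised arms is the Wilcoxon signed rank test, a paired or one-sample test; it should be the rank-sum test

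*Protocol article*

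**What the plan says.** The Statistical methods section of the protocol article sets out the analysis of continuous measures, with MADRS as the example, in two steps. First, "change scores will be calculated as the difference between baseline and 6-month visit assessments", which gives one number per patient. Then, "Groups will be compared using independent samples" t test or, as the alternative, "Wilcoxon signed rank test as appropriate". The following sentence, on binary measures, is also about the difference between the groups.

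The design sections show that these groups are unpaired. Under Allocation of interventions, "participants will be randomized to intervention and placebo control groups 1:1", using blocks of four. Under Intervention, "Each participant receives one dose of either autologous or allogenic FMT product". The article describes no matching of patients across arms and no crossover, and it does not name the rank-sum or Mann-Whitney test anywhere.

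**The concern.** The signed rank test is the non-parametric counterpart of the paired t test. It takes one difference per pair, or one sample of changes, and asks whether those values are centred on zero. The question in this sentence is whether two independent sets of change scores differ, and the signed rank test has no form that answers it.

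The choice between the two named tests is left to the analyst, so both need to be valid. The sentence covers every continuous outcome. Examining the effect on depression severity is part of the stated objective, and the Sample size section intends the between-group MADRS difference to inform a larger trial. If the fallback were used as named, the result would be either uncomputable, arbitrary, or an answer to a different question: whether patients improved, instead of whether the arms differ. In this design those two questions can easily have different answers. Entry requires a MADRS score of at least 20, so some regression to the mean is plausible, and both arms undergo bowel preparation and colonoscopy.

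**Working it through.** **Inputs from the protocol article.** 25 evaluable patients per arm; SD of MADRS change about 12 ("the expected standard deviation of change expected in the MADRS score is approximately 12"); 15% dropout; 30 recruited per arm (all from Sample size); two-sided 5% tests (Statistical methods).

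**The plan's own figure.** 25 / (1 − 0.15) = 29.4, rounded up to 30 per arm and 60 in total. This agrees with the article. It does not depend on the name of the test, so correcting the name leaves it unchanged.

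**What the named test does if followed literally.** There are three possibilities.

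1. *Unequal arms.* A paired routine given 26 values in one arm and 24 in the other stops with an error. Unequal arms are the likely case. If each of 30 patients per arm completes independently with probability 0.85, the chance of equal numbers is the sum over k of [C(30,k) × 0.85^k × 0.15^(30−k)]² = 0.145. The arms would therefore differ in size in about 85% of such trials.

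2. *Equal arms, paired arbitrarily.* One data set was simulated with 25 per arm, SD 12 and assumed mean improvements of 8 and 12 points. Over 2,000 random pairings of the same data, the signed rank p value ran from 0.14 to 1.00. The rank-sum test, which needs no pairing, gave a single p value of 0.59.

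3. *Run on the change scores.* The null hypothesis becomes no change from baseline. The simulations used normal data, 25 per arm, SD 12, and the same mean improvement in both arms, so that no between-arm difference exists. The size of that improvement is an assumption; the article gives none.

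| Assumed improvement in both arms (points) | Signed rank p < 0.05 within one arm |
|---|---|
| 4 | 35% |
| 6 | 66% |
| 8 | 88% |
| 10 | 97% |

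These come from 3,000 trials per row. Across the rows the rank-sum test rejected in 4.7% to 5.4%. A separate run of 4,000 trials at 8 points gave 87% within the allogenic arm, 99% for the signed rank test on both arms' changes pooled, and 4.9% for the rank-sum test.

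If the two within-arm results were then set against each other, they would often disagree by chance. At 6 points, one arm is significant and the other is not with probability 2 × 0.66 × 0.34 = 0.45; the simulated figure was 44%.

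**The case against.** The strongest reply is that this is a slip of the pen. The sentence says that the groups are compared, it sets the test beside the independent samples t test, and the next sentence again concerns a between-group difference. The intended analysis is clear, and with unequal arms the error would show itself as soon as anyone tried to run the test. That is probably right about intent. It does not make the named test valid, and nothing else in the article corrects it. An unseen analysis plan may name the right test, but this article names a specific test and names the wrong one.

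The reply also has force on impact, and most of that stands:

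- The test is a fallback. The t test beside it is valid, and the article also plans random effects and GEE models with group, time and group-by-time terms.
- The article says nothing about skewness of MADRS change, so there is no evidence that the fallback will be needed.
- The primary outcomes are feasibility, acceptability and adherence, and the Discussion says that the results will not support definitive conclusions on efficacy.

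A reader might infer from the table that the plan carries a false-positive rate of 35% to 97%. The documents do not support that. Those figures describe a within-arm test that the article does not assign to this comparison. They rest on an assumed improvement common to both arms, and they use normal data, for which the correctly named t test would be the natural choice.

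**Conclusion.** The statement is wrong as written: a paired or one-sample test is named for comparing two independent randomised arms. This conclusion rests only on the article's description of the design and of the comparison, and on no simulation.

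The size of the problem is minor to should-fix. The between-group efficacy comparison does not depend on the misnamed test, no stated figure changes, and the trial's primary questions are untouched. The simulated rejection rates show why the test must not be run on change scores and reported as a group comparison. They hold only under the stated assumptions (SD 12, 25 per arm, equal improvement of 4 to 10 points in both arms, normal data) and are not an estimate of this plan's error rate.

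**What to change.** In the Statistical methods section, for the between-group comparison of continuous change scores, name the Wilcoxon rank-sum (Mann-Whitney) test in place of the Wilcoxon signed rank test. Reporting the Hodges-Lehmann shift with a 95% confidence interval beside it would suit a pilot that aims at estimation, but it is optional and not needed to correct the error. If a within-arm signed rank test is also wanted, for instance for the baseline to study-completion comparison of clinical and tolerability scores, state it separately, label it descriptive, and do not use it to compare the arms.

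The cost is one phrase. Sample size, data collection and the other planned analyses stay as they are. The correction should be recorded before the analysis begins.

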To date, no clinical trials have investigated the feasibility and efficacy of FMT in individuals with BD, but a recent systematic review of preclinical and clinical work reported a decrease in depressive and anxiety-like symptoms and behaviours resulting from the transplantation of healthy microbiota, providing support for this area of research [15]. Herein, we present the methodology of a pilot randomized controlled study that evaluates the feasibility of a trial protocol for FMT in participants with BD depression.

The primary objective of this protocol is to evaluate the feasibility of FMT in a BD population and to also examine FMT efficacy in reducing depression severity in BD patients on stable, first-line treatment for BD depression with a prospective, double-blind randomized controlled trial (RCT). This will guide the development of a larger multisite RCT and further our understanding of the potential biotherapeutic potential of FMT. Other secondary objective of the pilot study are to determine the acceptability, safety, and tolerability of FMT in this population.

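### Side-effect proportions are to be compared between arms only by a 5% test; a risk difference with a confidence interval would serve the pilot's safety objective better

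*Protocol article*

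**What the plan says.** The Background of the protocol article gives as an aim: "Other secondary objective of the pilot study are to determine the acceptability, safety, and tolerability of FMT in this population". For binary data the Statistical methods section states: "For binary measures (e.g., proportion of side effects), the difference between groups will be tested using Chi-square or Fisher exact test as appropriate". It fixes the level for every test: "All tests will be two-sided with a significance level of 5" per cent. Multiplicity is left open: "Where necessary, *p* value adjustments for multiple testing". No effect estimate, interval or upper limit is stated for side effects or adverse events.

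The Sample size section uses a different logic for depression. It makes no formal power calculation because this is a pilot, and justifies the size by precision: "we will be able to quantify the difference in change in MADRS score between groups to within 6.5 points with 95% confidence". That rests on 25 evaluable patients per group; 30 per group are recruited to allow for 15% dropout.

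Other safety material is present. Statistical methods provides descriptive frequencies and proportions, a two-group test on change scores for continuous measures, and longitudinal models with a group-by-time term. The outcomes section compares tolerability scores at baseline with those at the last visit. A Data Monitoring Committee reviews serious adverse events. The Discussion says that a pilot cannot settle efficacy or safety.

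**The concern.** A pilot that informs a decision on a larger trial should say how much excess harm from donor stool is still compatible with its data. A test at 5% does not say that. With so few patients per arm, a non-significant p value is the likely result over a wide range of true differences, including a doubling or tripling of risk. It separates a harmless product from a moderately harmful one poorly.

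The arm comparison also has a limit by design. Both groups have bowel preparation, colonoscopy and instillation, so harm from the procedure falls on both sides and cancels. It can be seen only in the rate within each arm or over both arms together, and no bound is stated for those rates.

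**Working it through.** **Inputs from the protocol article.** Allocation is 1:1, with 25 evaluable and 30 randomised per arm. The test is Fisher or chi-square, two-sided at 0.05. The SD of MADRS change is about 12. No side-effect rates are given, so all rates below are assumptions.

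**The plan's own precision figure.** Half-width = 1.96 × SD × √(2/n) = 1.96 × 12 × √(2/25) = 6.65 points, or 6.82 with the t quantile on 48 df. The stated 6.5 is slightly optimistic, but within 2.3% of the normal value. For recruitment, 25/0.85 = 29.4, rounded up to 30. Both figures reproduce. There is no corresponding figure for harms.

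**Chance that the test misses a true difference.** For each n, every pair of event counts was enumerated and weighted by the two binomial probabilities. The miss rate is one minus the total weight of tables with p ≤ 0.05. Chi-square is without continuity correction.

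| Assumed rates (autologous v allogenic) | Fisher, n = 25 / 30 | Chi-square, n = 25 / 30 |
|---|---|---|
| 5% v 15% | 93% / 91% | 79% / 74% |
| 10% v 30% | 70% / 63% | 55% / 50% |
| 20% v 40% | 77% / 70% | 65% / 61% |
| 20% v 60% | 21% / 15% | 13% / 9% |

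Which column applies depends on expected counts (mean rate × n). For 5% v 15% these are 0.10 × 25 = 2.5 and 0.10 × 30 = 3, where Fisher would ordinarily be used. For 20% v 40% they are 0.30 × 25 = 7.5 and 0.30 × 30 = 9, where chi-square is usable.

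Five events against none does not reach significance by Fisher: p = 0.0502 at 25 per arm and 0.052 at 30. Any multiplicity adjustment would lower power further.

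**What an interval would show.** Newcombe 95% intervals for the risk difference, with assumed counts:

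- 0/30 v 0/30: −11.4 to +11.4 points; 0/25 v 0/25: −13.3 to +13.3.
- 6/30 v 6/30: −20.2 to +20.2 points.
- 6/30 v 3/30: −8.8 to +28.5 points (Fisher p = 0.47).
- 5/25 v 2/25: −8.3 to +32.0 points (Fisher p = 0.42).

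In the last two cases the p value alone would give no sign that an excess of nearly 30 points or more remains possible.

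**Upper limits when no event is seen.** The exact two-sided 95% limit is 1 − 0.025^(1/n). This gives 13.7% for 0/25, 11.6% for 0/30 and 6.0% for 0/60 (both arms pooled).

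**The case against.** The strongest reply has four parts.

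1. Chi-square and Fisher tests are standard for binary data, and the choice of interval is often left to an analysis plan or full protocol, neither of which is shown. The article does not exclude intervals, and they can be computed from the proportions it promises. This stands in part: nothing here is an error. But the article does more than stay silent. It names a test as the way the arms will be compared on side effects, and a better summary for the same data can be named.

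2. The test is not the whole safety analysis. This stands. Comparisons of change scores and the longitudinal models can cover continuous TSES scores. The models are worded generally enough to admit a binary outcome, but the article does not tie them to side-effect proportions or state a bound on those proportions.

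3. A reader might infer that a non-significant test would be taken as evidence of safety, or that such a result carries no information. The documents support neither. No section draws the first inference, and the Discussion disclaims firm conclusions on safety. As to the second, 20% v 60% is detected in 79-85% of trials by Fisher and 87-91% by chi-square, and zero events in both arms would exclude differences beyond about 11 to 13 points.

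4. The autologous control was chosen deliberately, because bowel preparation and colonoscopy themselves alter the microbiome. Procedure harms are captured by the symptom diary, adverse-event screening and committee review. This stands, so the shared procedure is not a design fault. It does mean that procedure-related harm needs a pooled summary rather than an arm comparison.

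**Conclusion.** The point holds as a low-cost improvement. For side-effect proportions the article states a two-sided 5% test and no estimate or interval, although safety is an objective and the MADRS comparison is planned by precision. Under the assumed rates, moderate excess harm is missed in about half of trials at best (10% v 30%, chi-square, 30 per arm) and in more than 90% at worst (5% v 15%, Fisher). A non-significant result would be weak evidence about safety. The miss rates depend on the assumed event rates, on 25 to 30 patients per arm contributing, and on which test is used. The zero-event limits depend only on the number of patients.

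**What to change.** In Statistical methods, make estimation the safety summary for binary data:

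- Report the allogenic-minus-autologous risk difference, with a 95% confidence interval (for example Newcombe), in the proportion of patients with at least one side effect or adverse event.
- Report exact 95% upper limits for serious and for related events in each arm, and pooled over both arms for procedure-related harm.
- Keep any chi-square or Fisher test as secondary, and say there that a non-significant result is not evidence of safety, in line with the Discussion.

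This changes analysis wording only and needs no new data or patients. The cost is presentational: the intervals will be wide and will look less favourable than a statement of no significant difference.

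### Chance imbalance seen between the randomised groups is allowed to steer which prognostic factors enter the longitudinal models, and none is adjusted for regardless of balance

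*Protocol article*

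**What the plan says.** All of this stands in the Statistical methods section of the protocol article.

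- A baseline check comes first: "Randomized groups will be compared to assess whether imbalance in covariates such as age and gender are present". No test or cut-off for imbalance is given.
- Change scores from baseline to 6 months are compared between groups without covariates. The covariate sentence does not touch that comparison.
- The longitudinal models (random effects and generalised estimating equations) have a fixed core: "All models will include group, time, and group by time interaction terms".
- Anything further is settled by this sentence: "factors with known influence on outcome measures will be considered for inclusion as covariates, particularly if found imbalanced between the randomized groups".

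The Sample size section sets no power target ("Therefore, no formal sample size calculation has been carried out"). It rests the trial size on the precision of the MADRS comparison. The assumed spread is put this way: "the expected standard deviation of change expected in the MADRS score is approximately 12". The precision claim built on it reads: "with 25 patients per group, we will be able to quantify the difference in change in MADRS score between groups to within 6.5 points with" (the level meant is 95%).

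**The concern.** In a randomised comparison, a baseline difference between arms is a product of chance. Its size does not show whether the covariate matters to the outcome. A strong predictor of MADRS change is worth adjusting for even when perfectly balanced, because it removes residual variance. A factor that predicts nothing is not worth adjusting for, however unbalanced it looks. Prognostic strength, judged in advance, should therefore decide.

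The protocol starts from that criterion and then adds a second one that can be applied only after the groups have been compared. Two things follow. The form of the efficacy model depends on the data and on the analyst's view of what counts as imbalanced. And prognostic factors that look balanced get lower priority, so available precision may not be used.

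This matters because the Background section makes efficacy on depression severity part of the primary objective, and the Sample size section says the MADRS data will be used to size a larger trial. The estimate carried forward should not depend on a choice made after seeing the allocation.

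**Working it through.** **Inputs from the protocol article.** SD of MADRS change 12; 25 evaluable per group; half-width 6.5 points at 95% confidence; 15% dropout; 60 recruited (Sample size). Two-sided 5% tests (Statistical methods). 1:1 allocation in blocks of 4 (Allocation of interventions).

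**Assumptions, because the article gives no values.** One continuous covariate whose correlation r with MADRS change is 0.3, 0.5 or 0.7; an effect of 9.6 points (9.6/12 = 0.8 SD); an imbalance trigger at baseline p below 0.05, 0.10 or 0.20.

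**Step 1: the plan's own figures.** Half-width = 1.96 × SD × √(2/n) = 1.96 × 12 × √(2/25) = 6.65 points, or 6.82 with the t quantile on 48 df. The stated 6.5 is reproduced to within about 2% (6.65/6.5 = 1.023). Recruitment: 25/0.85 = 29.4, rounded up to 30 per group, 60 in all, as stated.

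**Step 2: precision with prespecified adjustment.** The residual SD becomes 12 × √(1 − r²), so the half-width is about 6.65 × √(1 − r²):
- r = 0.3: 6.65 × 0.954 = 6.35
- r = 0.5: 6.65 × 0.866 = 5.76
- r = 0.7: 6.65 × 0.714 = 4.75

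Simulation with t-based intervals gives about 6.54, 5.94 and 4.90, to be set against the unadjusted 6.82.

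**Step 3: the limiting case in which imbalance alone decides entry.** 40,000 simulated trials per setting, 25 per group, one time point. Three analyses were compared: never adjust, adjust only if the baseline t test falls below the trigger, and always adjust. Ranges run over the three triggers; losses are taken before rounding.

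| r | Power, never adjust | Power, imbalance decides | Power, always adjust | Loss against always adjusting (points) | Type I error, imbalance decides |
|---|---|---|---|---|---|
| 0.3 | 79% | 80% | 82% | 2–3 | 4.6–4.8% |
| 0.5 | 79% | 80–82% | 88% | 7–9 | 3.8–4.4% |
| 0.7 | 79% | 81–85% | 97% | 12–16 | 2.6–3.7% |

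Always adjusting holds type I error at about 5%. The imbalance rule falls below 5% because it removes the worst chance imbalances but still reports the unadjusted standard error in the remaining trials. At r = 0.5 its mean reported half-width is 6.65 to 6.77, against 5.94 with prespecified adjustment.

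The true sampling SD of the estimate suffers less when the trigger is generous. At r = 0.5 and a trigger of 0.20 it is 3.39 unadjusted, 3.13 under the rule and 2.97 prespecified. At a trigger of 0.05 the figures are 3.41, 3.30 and 2.97. The loss is therefore mainly in the reported interval width and in power.

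**The case against.** The strongest reply is that known influence is the entry criterion and imbalance only adds weight to it. That is correct. A reader might infer that covariates enter purely according to observed imbalance, that balanced predictors are shut out, or that weak covariates can get in. The text supports none of these: balanced prognostic factors remain eligible, and a factor must have known influence to be considered. Step 3 above is therefore a limiting case and not the protocol's rule.

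A reader might also infer that imbalance just short of a cut-off goes uncorrected, or that false positives are inflated. The article states no imbalance test or cut-off, so the first has no object. The second is contradicted by the simulation, where overall type I error falls below 5%.

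The simulation uses a single time point and one covariate, whereas the covariate sentence governs repeated-measures models. The correlations are not documented, and the only examples named in the baseline check are age and gender, for which the article shows no strong association with outcome. At r = 0.3 the loss is small.

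The stakes are also limited. The listed primary outcome measures are feasibility, acceptability and adherence, there is no power target, and the Discussion disclaims definitive efficacy conclusions.

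Finally, a covariate list may properly sit in an analysis plan that is not shown, so its absence from the article is no fault. What stands is the stated criterion. An analysis plan that followed this sentence would carry the imbalance criterion with it, and one that did not would depart from the protocol.

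**Conclusion.** The point holds in a limited form. The protocol lets observed imbalance influence which prognostic factors enter the longitudinal models and commits to none regardless of balance. The consequence is discretion after the data are seen and possible loss of precision in the MADRS estimate meant to inform a larger trial. It is not an inflated error rate.

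How much precision is at stake depends on the assumed correlation: roughly 0.3, 0.9 or 1.9 points off a half-width of 6.65 at r = 0.3, 0.5 or 0.7 (6.65 − 6.35, 6.65 − 5.76, 6.65 − 4.75). How much of that would actually be forgone depends on how heavily imbalance is weighed, which the text leaves open. The power losses in the table apply only if imbalance alone decides, at an assumed 9.6-point effect. For a pilot without a power target, severity is minor to moderate.

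**What to change.** Delete the clause that gives extra weight to factors found imbalanced. Before unblinding, state that the models for MADRS and the other continuous scales adjust for the baseline value of the outcome, entered as a covariate with the post-baseline visits as the response. Add at most one or two prognostic factors that are already recorded, chosen for expected prognostic strength and kept whatever the observed balance. The names can go in the analysis plan, but the principle belongs in this sentence. Keep the baseline comparison descriptive, and label any further adjustment as a sensitivity analysis.

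The cost is a change of wording, one to three model degrees of freedom, and the loss of post hoc covariate choice. No new data are needed, since the baseline scores are already scheduled in Table 1.
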